#### Primary outcomes – substance use

Comparisons in prevalence of substance use will be made between Grade 10 students in intervention and control schools at follow up to determine intervention effectiveness for each outcome measure. Generalized linear models (generalized estimating equation (GEE approach)) will be used [58]. The GEE will cater for dichotomous outcome data, school clustering, levels of strategy implementation, and student or school characteristics that are potential confounding variables. Usual assumptions of linear regression will be tested (including linearity, independence, constant variance and normality), with variations from normality adjusted for using the robust variance estimator. For all outcome analyses, school will be included in the model as the clustering unit.

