#### Random allocation of schools

Once 32 schools have been recruited to the study, the sample will be stratified by engagement in a national government initiative directed at schools in disadvantaged areas [35], and school size (medium sized school 400–800; large sized school >800). Schools will then be randomly allocated in a 20:12 block design ratio to either the intervention or the control group. Neither schools, parents of students, nor students attending selected schools will be blinded to the school allocation.

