### Data collection procedures

#### Student outcomes

Baseline data will be collected via a student survey completed by all consenting students in Grade 7 in both intervention and control schools in the first year of the study. Follow up data will be collected from the same students in the fourth year of the study when the student cohort is in Grade 10 in the same season as baseline.

The student survey will take approximately 25 minutes to complete. Data collection staff will be recruited and trained to support students to complete the online survey during class time.

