### Sample size

Based on past research [7,56], and the pilot study results, an estimated 80% of students will consent to participate. Based on this, and an estimated loss of students to follow-up from Grade 7 to Grade 10 of 25% a cohort sample of 1,360 Grade 7 students and 1,020 Grade 10 students in the control condition, and 2,270 Grade 7 students and 1,700 Grade 10 students in the intervention condition, will be the subject of analysis. Assuming 80% power, a 5% significance level, an intra-cluster correlation of 0.01, and a Grade 10 control group smoking prevalence of 14% the study will be able to detect a 4.8% lower prevalence of smoking for the intervention group. For recent and risky alcohol consumption, assuming a Grade 10 control group prevalence of 36.2%, a 7.0% lower prevalence of consumption can be detected. For use of marijuana, assuming a Grade 10 control group prevalence of 25%, a 6.2% lower prevalence of use respectively can be detected for marijuana. Finally, for other illicit drugs, assuming a Grade 10 control group prevalence of 9.3%, a 3.9% lower prevalence of use can be detected for the intervention group.

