#### Secondary outcomes - resilience

Assuming resilience scores are not normally distributed (as with the data from the pilot study) comparison of median scores will be made post-test between Grade 10 students in intervention and control schools to determine intervention effectiveness. Linear regression models (GEE) will test differences in overall sub-scale levels of resilience factors (predictor variable being treatment group).

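### Effectiveness is assessed by post-test comparisons, and the stated models do not fix Grade 7 values or the two stratification factors as covariates.

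*Protocol article*

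**What the plan says.** The section on primary outcomes in the protocol article states: "Comparisons in prevalence of substance use will be made between Grade 10 students in intervention and control schools at follow up". The Abstract also describes the comparison as post-test, for all measures. For resilience, the section on secondary outcomes says that "comparison of median scores will be made post-test", followed by a linear GEE for which treatment group is the only predictor given.

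Two other sections show what is available to these models. Under Student outcomes: "Follow up data will be collected from the same students in the fourth year of the study", so each student followed up has a Grade 7 record. Under Random allocation of schools: "the sample will be stratified by engagement in a national government initiative directed at schools in disadvantaged areas", and also by school size (400–800 or above 800), before the 20:12 allocation.

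The primary GEE does allow for adjustment. It is to handle school clustering, the level of strategy implementation, and student or school features that might confound the comparison. It names no baseline variable and excludes none. None of the statistical analysis sections mentions Grade 7 substance use, Grade 7 resilience, initiative engagement or school size.

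**The concern.** A cohort design with stratified allocation supplies two sets of baseline information that predict the outcome: the student's own earlier value, and the factors on which schools were balanced. A model that fixes them in advance normally gives a tighter estimate and removes whatever chance difference in those variables the randomisation leaves. Here the resilience model as written omits them, and the substance-use model leaves their use undecided.

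With only 12 control schools, chance differences in school-level baseline values can be noticeable, and any that predict Grade 10 use carry into the Grade 10 contrast. Stratification limits this for the two stratifiers but not for Grade 7 use. There are also several primary outcomes, and an adjustment rule worded around possible confounding leaves the analyst a choice that is better closed before the data are seen.

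**Working it through.** **Inputs.** From Sample size: "Assuming 80% power, a 5% significance level, an intra-cluster correlation of 0.01, and a Grade 10 control group smoking prevalence of 14"%; 1,020 control and 1,700 intervention students in Grade 10. From Study design: 12 control and 20 intervention schools, so 1,020/12 = 1,700/20 = 85 followed students per school. The article does not say whether the test is two-sided; two-sided is taken here because it reproduces the figures.

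**The plan's own figure.** Design effect = 1 + (85 − 1) × 0.01 = 1.84. Effective numbers are 1,020/1.84 = 554 and 1,700/1.84 = 924. For 14% against 9.2%, the pooled proportion is 0.110:

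- SE under no difference = √[0.110 × 0.890 × (1/554 + 1/924)] = 0.0168
- SE under the alternative = √[0.14 × 0.86/554 + 0.092 × 0.908/924] = 0.0175
- Power = Φ[(0.048 − 1.96 × 0.0168)/0.0175] ≈ 0.805

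Solving for 80% power gives 4.77, 7.03, 6.19 and 3.88 points for smoking, alcohol, marijuana and other illicit drugs. The article states 4.8, 7.0, 6.2 and 3.9 (for example "the study will be able to detect a 4.8% lower prevalence of smoking for the intervention group"). The sample size is therefore an unadjusted follow-up comparison, and it is correct as such.

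**Gain from adjustment.** The article gives neither the correlation r between the baseline covariates and the Grade 10 outcome nor the share of the intra-cluster correlation (ICC) they would explain. Both are assumed over a range. In route (a) the variance is multiplied by 1 − r². In route (b) the ICC is reduced and the design effect becomes 1 + 84 × ICC.

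| Assumption | Detectable smoking difference (points) | Power at 4.8 points |
|---|---|---|
| No adjustment | 4.77 | 0.805 |
| (a) r = 0.1 | 4.75 | 0.808 |
| (a) r = 0.2 | 4.69 | 0.820 |
| (a) r = 0.3 | 4.57 | 0.839 |
| (a) r = 0.5 | 4.19 | 0.900 |
| (b) 25% of ICC explained (0.0075; design effect 1.63) | 4.52 | 0.848 |
| (b) 50% of ICC explained (0.005; design effect 1.42) | 4.24 | 0.892 |

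A cross-check on (b): the between-school share of the variance of a school mean is 0.01/(0.01 + 0.99/85) = 0.46. Explaining 25% or 50% of it leaves a variance factor of 1 − 0.46 × 0.25 = 0.885 or 1 − 0.46 × 0.50 = 0.77, and 4.8 × √factor gives about 4.5 or 4.2 points. The other three outcomes move in nearly the same proportion; alcohol, for example, goes from 7.03 to 7.00 at r = 0.1 and to 6.12 at r = 0.5. For resilience scores, an assumed Grade 7 to Grade 10 correlation of 0.3 to 0.5 would remove 0.3² = 9% to 0.5² = 25% of the individual-level variance.

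**Chance imbalance.** For a school-level baseline value, the arm difference has standard error √(1/20 + 1/12) = 0.37 school-level SDs, before any benefit of stratification. A gap above 0.3 SD has probability of about 41%, and above 0.5 SD about 17% (normal approximation). As a prevalence, with an assumed Grade 7 use of 5% and the same ICC of 0.01 on 1,360 and 2,270 students (about 113.5 per school, design effect 2.125), the standard error is √[0.05 × 0.95 × 2.125 × (1/1,360 + 1/2,270)] = 1.1 points. At 2% it is 0.7 points and at 10% it is 1.5 points.

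**The case against.** The strongest reply is that naming the follow-up time point does not make a model unadjusted. The provision for student and school features could admit Grade 7 use, initiative engagement and size, and an article commonly leaves the exact covariate list to the analysis plan. That stands for the primary outcomes. A reader might infer that the analysis ignores baseline data and strata altogether, but the text shows only that it does not fix them. The reply is weaker for resilience, where a sole predictor is stated. It is also incomplete for substance use, because the article does give an adjustment rule and that rule is open-ended.

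The second reply is that the gain may be negligible. Students are 12 to 13 at baseline, no Grade 7 prevalence is given, and rare use would predict little three years later. This stands too, and it is why the range above starts close to no gain.

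Third, stratified allocation already balances the two stratifiers. Omitting them tends to make standard errors conservative; it does not make the test invalid. That is correct.

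Two further readings are tempting but unsupported. The article does not say that the GEE will be restricted to complete cases, so the expected 25% loss to follow-up cannot be charged to this wording. Nor does it link its chi-square comparisons of the arms to the choice of covariates, so selection from observed imbalance is something the open rule permits but the article does not plan.

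**Conclusion.** The point holds as one of efficiency and pre-specification. The stated contrasts are post-test, and neither the Grade 7 values nor the two stratification factors are fixed in any model, although all are collected. A reader might go further and infer that the Grade 10 contrast is biased or that the sample size is wrong. Neither follows: randomisation makes the unadjusted contrast valid, and all four detectable differences reproduce.

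The benefit for smoking runs from almost nothing (4.77 to 4.75 points at r = 0.1) to about half a point (4.2 points at r = 0.5, or 4.24 with half of the ICC explained). In power at 4.8 points, that is from under 1 to about 10 percentage points. The range rests wholly on assumed values of r and of the ICC explained. Scaling a difference in proportions is also only an approximation to what an adjusted logistic GEE would deliver. Protection against chance imbalance and a closed covariate set are worth having even at the low end.

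**What to change.** Replace the open provision for possible confounders with a fixed primary model: allocated arm, the student's Grade 7 value of the same outcome (or the school's Grade 7 prevalence if use is rare), initiative engagement and size stratum, with school as cluster. Use the same model for each resilience subscale, with its Grade 7 score. Because a logit model with covariates estimates a conditional effect, state that the result will be reported on the marginal prevalence scale, which matches how the sample size is framed. The level of strategy implementation is measured after allocation and is a separate question from this baseline set.

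No new data are needed, but the change is not free. The two strata use 2 school-level degrees of freedom, and a school-level baseline term uses 1 more: from 32 − 2 = 30 down to 28 or 27. A rule for missing Grade 7 values must also be written.

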## Methods

### Study design

A cluster randomised control trial design (Figure 1) will be conducted, with schools as the unit of randomisation. Thirty two schools will be randomly selected to participate in the study, with 20 schools randomly allocated to the intervention group, and 12 to the control group. A resilience intervention will be implemented in schools allocated to the intervention group. Schools allocated to the control group will not receive any intervention during the study period. To assess the efficacy of the intervention, baseline web-based surveys will be conducted with Grade 7 students. Follow up data will be collected using the same method three years later when the original cohort of students are in Grade 10.

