### Resilience intervention

#### Intervention content

A multi-strategy intervention, based on a range of programs and strategies that address both internal and external adolescent resilience factors will be implemented for the whole school. Schools will be asked to implement a range of strategies in each of the Health Promoting Schools domains (curriculum, teaching and learning; ethos and environment; and partnerships and services) to enhance student resilience [37]. The strategies schools select will be informed by a comprehensive and structured planning process and will be selected from a list of evidence based programs (eg. MindMatters program). In this manner, the strategies implemented by each school may differ. However, schools will be asked to implement strategies to an intervention standard (see Table 1).

**Table 1 T1:** Resilience intervention standards

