### Intervention adoption strategies

To increase the extent of intervention adoption and fidelity across schools, a number of strategies will be implemented that have been previously reported to facilitate adoption of school-based interventions, to change the service delivery practices of human service organizations, and to build capacity of organisations [17,31,39-44].

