#### School outcomes

At baseline and follow up, a school environment survey will be undertaken with key school staff including principals and head teachers of both intervention and control schools to identify existing school policies and practices that target student resilience.

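### The primary GEE takes in levels of strategy implementation without limiting them to baseline; in-trial levels are what allocation is meant to change, so adjusting for them would remove part of the effect

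*Protocol article*

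**What the plan says.** The section on primary outcomes (Statistical analysis) sets the purpose of the comparison: "Comparisons in prevalence of substance use will be made between Grade 10 students in intervention and control schools at follow up to determine intervention effectiveness". It then names a GEE and lists what that model handles: "The GEE will cater for dichotomous outcome data, school clustering, levels of strategy implementation, and student or school characteristics that are potential confounding variables". No separate dose-response, per-protocol or mediation analysis is described. For the secondary resilience outcomes, by contrast, treatment group is the only predictor named.

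Other sections show what implementation is:

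- Intervention content: "Schools will be asked to implement a range of strategies in each of the Health Promoting Schools domains", and "schools will be asked to implement strategies to an intervention standard" (Table 1).
- The same section allows variation between schools: "the strategies implemented by each school may differ".
- Intervention adoption strategies: "To increase the extent of intervention adoption and fidelity across schools, a number of strategies will be implemented".
- Study design: "Schools allocated to the control group will not receive any intervention during the study period".

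Implementation is recorded more than once. The eligibility interview under School recruitment asks principals what resilience strategies are already in place. The school environment survey, run in both arms at baseline and again at follow-up, serves "to identify existing school policies and practices that target student resilience".

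**The concern.** A covariate in a randomised comparison is harmless if its value is fixed before allocation. Implementation during the trial is not. Schools in one arm are asked and funded to raise it, and schools in the other are not, so it lies on the path from allocation to substance use.

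Putting it in the model that judges effectiveness has three consequences:

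1. The arm coefficient no longer estimates the total effect of being allocated to the programme. At best it estimates whatever effect does not pass through implementation.
2. Implementation follows arm closely if the programme is taken up, so the two school-level terms compete for the information in 32 schools and the standard error grows.
3. Schools choose their strategies. Factors such as leadership or student mix may drive both implementation and substance use, and conditioning on implementation lets them bias a contrast that randomisation had protected.

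At stake is the primary result on every substance-use outcome: a programme that works could be reported as having little or no effect.

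**Working it through.** **Inputs from the protocol article (Study design; Sample size).** 12 control and 20 intervention schools; 1,020 and 1,700 Grade 10 students, so 1,020/12 = 1,700/20 = 85 per school; ICC 0.01; 5% significance; 80% power; control smoking 14%, detectable difference 4.8 points.

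**Step 1: reproduce the plan's own figure.** Design effect = 1 + (85 - 1) × 0.01 = 1.84. Effective numbers are 1,020/1.84 = 554.3 and 1,700/1.84 = 923.9. For 14% against 9.2%:

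- pooled prevalence = 0.375 × 0.14 + 0.625 × 0.092 = 0.110
- null SE = √[0.110 × 0.890 × (1/554.3 + 1/923.9)] = 0.0168
- alternative SE = √[0.14 × 0.86/554.3 + 0.092 × 0.908/923.9] = 0.0175
- power = Φ[(0.048 - 1.96 × 0.0168)/0.0175] = 80.5%

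The same method gives detectable differences of 4.77, 7.03, 6.19 and 3.88 points for smoking, alcohol, marijuana and other illicit drugs, against the stated 4.8, 7.0, 6.2 and 3.9. The sample size section is sound. Its figures describe a comparison of arms with no implementation term.

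**Step 2: the effect on the log-odds scale.** ln(0.092/0.908) - ln(0.14/0.86) = -2.289 + 1.815 = -0.47.

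**Step 3: what the extra term does, by approximation.**

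- *Bias.* If a share f of the effect acts through implementation, the adjusted coefficient is about (1 - f) × (-0.47): -0.47 at f = 0, about -0.24 at f = 0.5, and 0 at f = 1.
- *Precision.* If implementation correlates r with arm across schools, the SE grows by about 1/√(1 - r²): 1.15 at r = 0.5, 1.40 at r = 0.7, 2.11 at r = 0.88.

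**Step 4: simulation.** The implementation scores are assumptions; the document gives none. Both simulations fit logistic GEEs with school-robust variance, 12 against 20 schools, ICC 0.01 and smoking 14% against 9.2%.

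- Simulation A: 6,000 trials, school sizes varying around 85 (CV 0.4), independence working correlation, mean implementation 20% against 70%, r = 0.88, full mediation.
- Simulation B: 400 trials per scenario, 85 per school, exchangeable correlation, mean score 0.2 against 0.8, SD 0.15. Before truncation to the 0–1 range, r² = (0.375 × 0.625 × 0.6²)/(0.375 × 0.625 × 0.6² + 0.15²) = 0.0844/0.1069 = 0.79, so r = 0.89.

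| Scenario | Log OR (SD), term left out | Rejects | Log OR (SD), term included | Rejects |
|---|---|---|---|---|
| A, all mediated | -0.47 (0.18) | 78% | +0.04 (0.40) | 7–10% |
| B, all mediated | -0.46 (0.19) | 75% | +0.06 (0.41) | 7.5% |
| B, half mediated | -0.48 (0.19) | 75% | -0.24 (0.46) | 18% |
| B, no effect | -0.01 (0.16) | 8.5% | +0.02 (0.38) | 10% |

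The simulated SDs agree with Step 3 (A: 0.18 × 2.11 = 0.38). The last row shows that 7–10% is about the rate at which this robust-variance GEE rejects when there is no effect at all. Neither simulation includes a school factor that drives both implementation and smoking, so confounding of that kind would come on top, in an unknown direction.

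**The case against.** The strongest reply is that the sentence may not mean what it seems to. *Cater for* is looser than *adjust for*, and two of the four listed items (binary outcome, clustering) are not covariates. The comparison itself is defined by arm. Implementation is also recorded before or at baseline, through the eligibility interview and the baseline school survey. Only schools already running a comprehensive programme are excluded, so recruited schools may differ in what they do beforehand, and that pre-allocation level would be a legitimate covariate.

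Much of this stands. A reader might infer that the plan definitely adjusts for a value measured after randomisation; the document does not establish that, because the time point is not given. It does not remove the problem. The same verb covers clustering and confounders, which are handled within the model, so a model term is the natural reading. Nothing limits it to baseline, and the wording matches the description of what intervention schools will do. Nor is this a detail left to an analysis plan: the article itself names the variable in the primary model.

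A second reply is that the near-null result is built in by assuming full mediation and a correlation near 0.9 with arm. That is correct. It is the extreme case, which is why the half-mediated case and the range of r are shown.

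A reader might also extend the point to the items on beliefs about harm under Primary outcome measures. The document calls those moderators and does not say that they enter this model, so the extension has no support.

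**Conclusion.** The point holds as a conditional one. As written, the primary GEE admits in-trial implementation as a model term, and following the text on its natural reading would condition the effectiveness contrast on a consequence of allocation. The direction rests on the document alone: the mediated share is removed and precision falls to the extent that implementation tracks arm. The size rests on assumed scores of about 0.2 against 0.7–0.8 and on the mediated share. For smoking, 75–78% power drops to 18% if half the effect is mediated and to about the no-effect rate if all of it is. With no mediation there is only loss of precision.

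A reader might conclude that the primary coefficient cannot estimate the intervention's effect, or that a null result is to be expected. The document does not support either: a baseline-only term would be harmless, and the mediated share is unknown. The sentence still needs correcting before analysis, because it permits the harmful version.

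**What to change.** In the section on primary outcomes, do one of two things:

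- remove implementation level from the list of what the primary GEE handles; or
- state that only the pre-allocation or baseline implementation level is used.

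On either route, keep allocated arm, school clustering and baseline covariates in the primary model. Report in-trial or follow-up implementation in a separate analysis, labelled as an exploratory dose-response or mediation analysis and not used to judge effectiveness.

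The cost is one or two sentences. No data collection changes, the sample size calculation stands, and the implementation question is still answered.

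### The primary GEE names only the robust variance estimator for 12 v 20 schools and assigns it to non-normality; used uncorrected with a Wald z test, it would reject above the nominal 5%

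*Protocol article*

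**What the plan says.** Study design fixes the clusters, "with 20 schools randomly allocated to the intervention group, and 12 to the control group", and Random allocation of schools adds two school-level stratification factors: "the sample will be stratified by engagement in a national government initiative directed at schools in disadvantaged areas [35], and school size".

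Primary outcomes – substance use plans a GEE for dichotomous outcomes with school as the clustering unit. The model is also to account for levels of strategy implementation and for student or school confounders, whose number is not given. The section continues: "Usual assumptions of linear regression will be tested (including linearity, independence, constant variance and normality", and then "with variations from normality adjusted for using the robust variance estimator". It names no other variance method, and it states neither a reference distribution nor a Wald or score test.

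Sample size rests on "Assuming 80% power, a 5% significance level, an intra-cluster correlation of 0.01" and gives detectable differences of 4.8, 7.0, 6.2 and 3.9 points for smoking, alcohol, marijuana and other illicit drugs.

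**The concern.** Two things are wrong in the analysis paragraph, and they are linked.

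- **The stated purpose.** The outcomes are yes/no. Their variance follows from the mean, so there is no normality or constant-variance assumption to check. Independence within schools is already given up by clustering on school. In a GEE the robust estimator protects the standard errors when the working correlation is wrong. It does not repair non-normality.
- **The protection needs many clusters.** With 32 schools, 12 of them in one arm, the uncorrected estimator is biased downwards. The bias grows with each school-level covariate. A normal or chi-square reference adds to the problem by ignoring that the variance is estimated from few schools.

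At stake are the 5% level and the width of the confidence intervals for every primary outcome.

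**Working it through.** **Inputs.** From the article: 12 and 20 schools; 1,020 and 1,700 analysed students, so 1,020/12 = 1,700/20 = 85 per school; ICC 0.01; 80% power; 5% level (taken as two-sided, since sidedness is not stated); control prevalences 14%, 36.2%, 25% and 9.3%. Assumed: school-size coefficient of variation (CV) 0, 0.4 or 0.6, and 0 to 6 school-level covariates.

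**Step 1: reproduce the plan's figures.** Design effect = 1 + (85 − 1) × 0.01 = 1.84. Effective sizes are 1,020/1.84 = 554.3 and 1,700/1.84 = 923.9. The detectable difference d solves

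d = 1.96 √[p̄(1−p̄)(1/554.3 + 1/923.9)] + 0.8416 √[p₁(1−p₁)/554.3 + p₂(1−p₂)/923.9], with p₂ = p₁ − d and p̄ the weighted mean.

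For smoking: 1.96 × 0.01682 + 0.8416 × 0.01755 = 0.0477. The same formula with t(30) quantiles (2.042 and 0.854) gives the last column.

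| Outcome | Stated | Recomputed, normal | With t(30) |
|---|---|---|---|
| Smoking | 4.8 | 4.77 | 4.9 |
| Alcohol | 7.0 | 7.03 | 7.3 |
| Marijuana | 6.2 | 6.19 | 6.4 |
| Other illicit drugs | 3.9 | 3.88 | 4.0 |

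All four figures reproduce, with the normal reference.

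**Step 2: why the level is exceeded.** Take equal school sizes, no covariates and a linear approximation. The uncorrected variance recovers on average 11/12 of the control part and 19/20 of the intervention part. The ratio to the true variance is [(1/12)(11/12) + (1/20)(19/20)] / (1/12 + 1/20) = 0.1239/0.1333 = 0.929, so the standard error is about √0.929 = 0.964 of what it should be. The 1.96 cut-off then acts like 1.96 × 0.964 = 1.89. On t(30) the two-sided tail beyond 1.89 is about 6.9%, against 5.9% beyond 1.96 from the reference distribution alone.

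**Step 3: simulation under no effect.** School counts were beta-binomial with ICC 0.01, and the model was a logistic GEE with 8,000 to 10,000 runs per setting. Monte Carlo standard error is about 0.26 points near 7% (√(0.07 × 0.93/10,000)) and 0.34 near 10% (√(0.10 × 0.90/8,000)). The covariates were unrelated to arm and outcome. The t reference has 32 minus the number of model parameters as degrees of freedom. The first row covers all four prevalences; the others cover 14% and 36.2%. Entries are rejection rates (%) at nominal 5%.

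| Setting | Robust, Wald z | Robust, t | Kauermann-Carroll, t | Mancl-DeRouen, t | Score |
|---|---|---|---|---|---|
| Equal sizes, 0 covariates | 7.1–7.3 | 6.0–6.2 | 5.0–5.4 | 4.1–4.5 | 4.8–5.4 |
| CV 0.4, 0 covariates | 6.6–6.8 | 5.6–5.7 | 4.7–5.0 | 3.9–4.4 | 4.6–4.9 |
| CV 0.4, 2 covariates | 8.1–8.6 | 6.9–7.3 | 5.4–5.5 | 3.7–4.0 | 5.6–5.9 |
| CV 0.4, 4 covariates | 10.0–10.2 | 8.6–8.8 | 5.6–6.0 | 3.4–3.6 | 6.9–7.1 |
| CV 0.6, 4 covariates, independence working correlation | 11.4–11.6 | 9.8–9.9 | 6.3 | 3.4–3.5 | 7.2–7.3 |
| CV 0.4, 6 covariates | 11.3–11.8 | 9.3–10.2 | 5.4–5.9 | 2.7–2.9 | 7.4–8.0 |

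A separate simulation of the Wald z test at the same ICC gave 6.6–7.6% with no covariates, 8–9.5% with two and 9.4–9.9% with four.

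**The case against.** The article never says that the robust variance is uncorrected, or that the test is Wald on a normal reference. Corrections and degrees of freedom are details that an article commonly leaves to the analysis plan, which is not shown. A reader might infer that the primary tests will reject 7–11% of the time. The document does not support that as a flat statement. Rates around 10% or more need four or more school-level covariates, and the article fixes no number. Student-level covariates do not use up school-level degrees of freedom in the same way. A score test, equally compatible with the text, stays near 5% unadjusted. This objection stands, and it makes the size conditional.

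It does not remove the point. The article does choose a variance method and gives it a wrong purpose, so that text needs correcting whatever the analysis plan adds.

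The linear-regression checks could belong to the linear GEE models for resilience scores under Secondary outcomes. They are nevertheless written into the paragraph on dichotomous outcomes. That misplacement is a wording fault and does not itself raise the false-positive rate.

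A reader might also infer that the sample size is wrong. It is not: the stated figures reproduce, normal quantiles are a conventional planning approximation, and t(30) moves them by only 0.1 to 0.3 points.

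**Conclusion.** The point holds in conditional form. The robust estimator is the only variance method named for the primary GEE, with 12 and 20 schools, and its stated purpose does not fit yes/no outcomes. Used uncorrected with a Wald z test, a nominal 5% test would reject about 7% of the time with no school-level covariates, about 8–9% with two (the number of stratification factors), and about 10% or more only with four or more. Confidence intervals built the same way would be correspondingly too short. A t reference without a variance correction helps only in part (5.6–10.2%), and a score test inflates less (4.6–8.0%).

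These sizes rest on ICC 0.01, 85 students per school on average, the assumed variation in school size, and simulated covariates that were not tied to the stratified allocation.

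**What to change.** - For every primary GEE, specify a small-sample-corrected sandwich variance with a t reference on schools minus school-level parameters. Kauermann-Carroll is preferred: it rejected 4.7–6.3% across the settings above. Mancl-DeRouen is conservative once covariates enter (2.7–4.0%), which costs power. A school-level analysis or a permutation test is an acceptable alternative.
- Delete the normality and constant-variance checks for the dichotomous outcomes, and describe the robust variance as protection against a misspecified working correlation.
- Optionally, restate the detectable differences on t(30) as about 4.9, 7.3, 6.4 and 4.0 points.

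No cap on school-level covariates is needed to resolve this point, though each one added makes the correction matter more. The cost is a change of wording and a change in how the variance is computed, with slightly wider confidence intervals. Design and data collection are unaffected.
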